## Abstract

Supplemental Digital Content is available in the text

## Introduction

1

Circulatory disturbance manifests as various symptoms caused by reduced blood flow from blood clotting or changes in blood composition. There are 2 types of circulatory disturbances: hemorrhage, meaning escape of blood from the blood vessels, and ischemia, meaning failure/restriction of blood flow to a particular part of the body.^[1]^ Probable conditions leading to circulatory disturbances include hypertension, cardiovascular diseases, diabetes, hyperlipidemia, and arteriosclerosis, which cause complications, such as angina, dementia, and paralysis.^[2–4]^

Typically, blood stasis refers to the condition in which blood in the body does not flow inside the blood vessels, which are obstructed, or in which body fluids are found in an area outside their original position. In oriental medicine, it is believed that blood stasis cuts off communication within the meridian pathways and causes diseases.^[5–8]^ Particularly, chronic and incurable diseases, such as pain, infertility, and cancer, and diseases caused by stress cannot be treated with modern medicine, and are associated with blood stasis.^[5,6]^ However, the current concept of blood stasis is unclear. Therefore, through studies on blood stasis, it is essential to establish a foundation for oriental medical treatment by identifying a highly scientific part from the traditional concept of blood stasis, defining this part scientifically and clearly, reinterpreting the relevant diseases from the modern viewpoint, and providing a standard for the diagnosis of chronic and incurable diseases.^[6,7]^

Blood stasis refers to all pathological conditions resulting in aggregation and modification of the red blood cells, which can cause hematological changes, such as an increase in blood viscosity and reduction in blood flow velocity.^[6,8,9]^ Therefore, all diseases caused by these conditions are referred to as blood stasis, and blood stasis can be modernly reinterpreted by scientifically clarifying the concepts of blood and blood vessels.

In Korea, the prevalence of metabolic diseases in people aged ≥30 years is 28.8% (ie, 1 out of 3 people). The average prevalence rate of metabolic diseases (including hypertension, diabetes, hypercholesterolemia, and cancer) has increased by 1.8%, from 16.1% in 2007 to 17.9% in 2013, and this trend is particularly high in individuals aged ≥60 years.^[10]^ Treating blood stasis is effective in treating obesity and metabolic diseases in traditional Korean medicine.^[8,11]^

This prospective observational study with an exploratory purpose is aimed at designing a Korean medicine diagnostic technique for metabolic diseases with blood stasis, particularly circulatory disturbances, to explore the related Korean medicine treatment options and evaluate their validity by analyzing clinical data.

## Participants and methods

2

### Study aims

2.1

This exploratory study is aimed at designing a Korean medicine diagnostic technique for metabolic diseases with blood stasis, particularly circulatory disturbances, to explore the related Korean medicine treatment options and evaluate their validity by analyzing clinical data and blood samples.

### Study design/setting

2.2

This is a prospective observational study. We will recruit patients from the Dongguk University Ilsan Oriental Hospital (Ilsan) (Fig. 1). Table 1 shows the data collection and follow-up schedules.

**Figure 1 F1:**
[figure not shown]
A flow chart of the study. ABI = ankle-brachial index, baPWV = brachial-ankle pulse wave velocity, BMI = body mass index, BP = blood pressure, Visit 1 = 7 days after screening, WC = waist circumstance.

**Table 1 T1:**
[figure not shown]
Schedule of study visits and assessments.

### Study registration

2.3

This study is registered with the Clinical Research Information Service (https://cris.nih.go.kr/cris/en/): KCT0003548. Current protocol versions are 1.2.

### Eligibility criteria

2.4

#### Inclusion criteria

2.4.1

We will include patients who are eligible according to the following criteria:

1.Individuals aged between 20 and 70 years.2.Individuals who voluntarily sign the informed consent form for the clinical study, or those who are incapable of providing voluntary agreement but whose legal representatives sign the informed consent form.3.Individuals who are willing to cooperate and comply with regulations during the study period.4.Individuals who consent for blood collection for the purpose of this study.

For the study participants who meet the aforementioned criteria, the selection criteria for each group are as follows:

1.Ankle–brachial index (ABI) <0.9 or triglycerides ≥150 mg/dL and high-density lipoprotein cholesterol <40 mg/dL in men and <50 mg/dL in women2.Blood stasis score (≥9 points out of 32 total points)Group I (circulatory disturbance I): Meets both aforementioned criteria (1 and 2).Group II (circulatory disturbance II): Meets one of the aforementioned criteria (1 but not 2).Group III (normal): Does not meet either criterion from the aforementioned criteria.

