#### Exclusion criteria

2.4.2

1.Individuals with mental illness or those unable to communicate2.Critically ill patients who are unconscious and unable to communicate3.Pregnant patients4.Individuals currently on oriental medicine for the treatment of blood stasis5.Individuals presenting with any other condition that could influence the assessment of this study, based on the investigator's discretion

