### Statistical analysis

2.10

A basic analysis of the study results will compare the difference in evaluation indicators of groups I and II (with circulatory disturbances) with that of group III (without circulatory disturbances) at visit 1. All statistical analyses will be subjected to two-tailed tests, and the significance level will be set at 5%. A descriptive analysis of the evaluation items and blood indices for each group will be conducted to represent the categorical variables as n (%) and continuous variables as mean ± standard deviation. To compare the intergroup differences for the obtained outcome value for each item, categorical variables will be subjected to the chi-square test and Fisher exact test, whereas continuous variables will be analyzed using the *t* test and analysis of variance or nonparametric methods such as Mann-Whitney *U* test and Kruskal-Wallis test for those not meeting the normality criteria. Analysis of covariance will be performed when it is necessary to control underlying variables, such as demographic variables (sex, age, weight, and height). For data with a missing value, the last observation carried forward will be used through CRF inspection to replace the missing value.

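### The three groups leave out people with blood stasis but no circulatory disturbance, so only Group I vs Group II can show a blood stasis effect, and section 2.10 does not name that contrast

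*Protocol article*

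**What the plan says.** Section 2.4.1 of the protocol article lists four general inclusion criteria (age, consent, cooperation, consent to blood collection) and then continues: "For the study participants who meet the aforementioned criteria, the selection criteria for each group are as follows". Criterion 1 is "Ankle–brachial index (ABI) <0.9 or triglycerides ≥150 mg/dL and high-density lipoprotein cholesterol <40 mg/dL in men and <50 mg/dL in women". Criterion 2 is a blood stasis score of at least 9 out of 32. Group I meets both criteria, Group II meets 1 but not 2, and the third group is defined as "Group III (normal): Does not meet either criterion from the aforementioned criteria".

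Among the exclusions in section 2.4.2, the one closest to this point is "Individuals currently on oriental medicine for the treatment of blood stasis". It concerns current treatment, not the score. The last exclusion is a discretionary one for other conditions that could influence the assessment.

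Section 2.10 gives the task of the basic analysis as follows: "compare the difference in evaluation indicators of groups I and II (with circulatory disturbances) with that of group III (without circulatory disturbances) at visit 1". It then allows t tests, analysis of variance or rank tests for differences between groups, and analysis of covariance for sex, age, weight and height where needed. It does not name Group I vs Group II. Section 2.1 gives the aim as a diagnostic technique for metabolic diseases with blood stasis. Section 2.7.1 lists four blood markers as candidate indicators for diagnosing blood stasis, together with the blood stasis score, as primary outcomes.

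**The concern.** Two yes/no criteria make four combinations, and the article defines three. A person with a score of at least 9 but without criterion 1 meets the general criteria, is not named in any exclusion and has no group. The article does not say whether such a person is turned away or enrolled without a group.

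The larger consequence is for the analysis. Blood stasis occurs in the study only together with criterion 1, while the primary markers are candidates for detecting blood stasis. A marker that responds to low ankle-brachial index or to abnormal lipids, and not to blood stasis, will differ between I and II combined and III, between I and III, and between all stasis-positive and all stasis-negative participants. If any of these is read as evidence about blood stasis, the study may recommend a marker for the wrong condition. The one contrast that avoids this is available in the design but is not singled out.

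**Working it through.** The article states no effect size or power, so there is no figure of its own to reproduce.

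**1. Map the groups to the combinations (section 2.4.1).**

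| Criterion 1 | Criterion 2 | Group |
|---|---|---|
| yes | yes | I |
| yes | no | II |
| no | no | III |
| no | yes | none |

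**2. What can be estimated.** Write the mean of a marker as m in Group III, m + a in Group II and m + a + b in Group I. Here a is the criterion 1 effect without blood stasis, and b is the blood stasis effect given criterion 1. Let b0 be the blood stasis effect without criterion 1, so that the undefined combination has mean m + b0 and the interaction is b − b0.

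- The three groups give three means. A model with both criteria and their interaction has four parameters, so its rank is 3 of 4.
- Estimable: b (I − II) and a (II − III).
- Not estimable: b0, the interaction, and the criterion 1 effect in people with blood stasis (a + b − b0).
- With a fourth group the rank is 4 of 4 and all of these become estimable.

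**3. What each comparison measures.** Equal groups are assumed for the averages.

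| Comparison | Expected difference | If blood stasis has no effect (b = 0) |
|---|---|---|
| I and II vs III (named in 2.10) | a + b/2 | a |
| I vs III | a + b | a |
| I vs II and III pooled | b + a/2 | a/2 |
| I vs II | b | 0 |

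Derivation of the first row: [(a + b) + a]/2 − 0 = a + b/2. Third row: (a + b) − (a + 0)/2 = b + a/2. Only I vs II is free of a. Unequal groups change the weights of one half, but not this conclusion.

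**4. The score itself.** Group III is selected to score below 9, and so is Group II, while Group I scores 9 or more. The blood stasis score is a primary outcome, so differences in it between groups are partly or wholly set by the selection rule. I vs II is informative for the blood markers, not for the score.

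**5. Precision of I vs II.** Section 2.9 gives 100 participants in total and no split, so group sizes are assumptions. For a marker in SD units, SE = √(1/n₁ + 1/n₂), and the difference detectable with 80% power (two-sided 5%) is about 2.8 × SE.

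- Three equal groups of 33: √(2/33) = 0.246; detectable 2.8 × 0.246 = 0.69 SD.
- Four equal groups of 25: √(2/25) = 0.283; detectable 2.8 × 0.283 = 0.79 SD.
- Power for a true difference of 0.5 SD: 53% with 33 per group, 42% with 25. For 0.7 SD: 81% and 70%.

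The 100 is a recruitment target set with dropout in mind, so the analysed groups may be smaller than these.

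**The case against.** The aim concerns metabolic disease with blood stasis, for which the natural comparator is metabolic disease without blood stasis. That is Group II. People with blood stasis and no metabolic or vascular abnormality lie outside this target, and leaving them out may be deliberate. The article calls its rules selection criteria for each group, so someone who fits no group may simply not be enrolled. The general tests in section 2.10 permit I vs II. The study is exploratory, and a fourth group would thin the contrast that matters most.

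Most of this stands, and it rules out several stronger readings.

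- A reader might infer that the blood stasis effect cannot be separated from circulatory disturbance at all. That is not so: I and II both meet criterion 1 and differ on criterion 2.
- A reader might infer spectrum bias, with the hardest non-cases removed from the controls. The omitted people are positive on the blood stasis score, so they are non-cases only for criterion 1. Nor are the controls free of symptoms, since they may have any score below 9.
- A reader might blame the missing combination for the I vs III difference. Those two groups hold the same people whether or not a fourth is recruited.
- A reader might infer that a fourth group improves precision at the same total. The criterion 2 effect adjusted for criterion 1 would have SE √(1/50 + 1/50) = 0.20 with four groups of 25, but only if there is no interaction. Without that assumption, I vs II becomes less precise.

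The objection does not remove the mismatch between the markers' stated purpose and the named comparison. Tests that permit I vs II do not identify it as the blood stasis contrast, and an overall test across three groups does not isolate it. Nor does the article say that the fourth combination is not enrolled.

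**Conclusion.** The point holds in a limited form. Section 2.4.1 leaves one of four combinations without a group or a stated exclusion. As a result, blood stasis can be studied only within circulatory disturbance, and neither its effect outside that setting nor the interaction can be estimated. The comparison named in section 2.10 measures criterion 1 status, with controls also selected for a low score. It cannot show whether a marker indicates blood stasis: when blood stasis has no effect, it still returns the whole criterion 1 effect a.

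The mapping and the estimability results follow from the text alone. They do not depend on how the words or and and in criterion 1 are grouped, because any reading leaves the same fourth combination. The standard errors rest on assumed equal groups. The size of a for each marker is unknown, so the amount of confounding cannot be stated. Recruiting a fourth group is a trade-off for the sponsor and not a necessary correction; naming the right contrast is needed either way.

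**What to change.** **Section 2.10.** For each blood marker, define the blood stasis contrast as the effect of criterion 2 adjusted for criterion 1. With the three stated groups this is I vs II, using the covariates already listed where adjustment is needed. State that I and II vs III, and I vs III, will not be interpreted as evidence about blood stasis, and that conclusions on blood stasis are limited to people with circulatory disturbance. This costs a few sentences and no participants or measurements.

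**Section 2.4.1.** State that people who meet criterion 2 but not criterion 1 are not enrolled. Alternatively, add them as Group IV within the 100 and fit both criteria with their interaction. The second option makes the blood stasis effect without circulatory disturbance estimable. It requires an amendment and a source of such people, whose number the article does not give. It also raises the standard error of I vs II from about 0.25 to about 0.28 SD under equal groups of 33 or 25.

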#### Exclusion criteria

2.4.2

1.Individuals with mental illness or those unable to communicate2.Critically ill patients who are unconscious and unable to communicate3.Pregnant patients4.Individuals currently on oriental medicine for the treatment of blood stasis5.Individuals presenting with any other condition that could influence the assessment of this study, based on the investigator's discretion

### Recruitment

2.5

The researcher will explain the aim of this study and the details of the procedures and will obtain informed consent from potential subjects prior to the collection of information. Participants will be free to withdraw at any time during the study, and this will not affect their clinical treatment. We encourage voluntary participation in this clinical study that uses human biological material, by posting recruitment posters on the walls of the entrance and elevators of the hospital and through newspapers and bus advertisements.

### Intervention

2.6

Since this is an observational study, the treatment to improve circulatory disturbance is not restricted during the study. For a given period, treatment with Korean medicine, other Korean medical treatment, and prescription medication other than Korean medicine should be recorded. For Korean medicine, the name of the medicine, medicine composition, and treatment duration should be recorded.

For participants enrolled in the study after screening, we will perform blood tests; ABI and brachial–ankle pulse wave velocity measurement; blood stasis diagnosis questionnaire assessment; blood pressure, body mass index, and waist circumference measurement; and concomitant drug and Korean medical treatment assessment at visit 1 within 7 days of registration.

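### Grouping ignores current lipid-modifying treatment, so treated would-be Group II members can be classed as normal controls

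*Protocol article*

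**What the plan says.** Section 2.4.1 of the protocol article sets two grouping criteria. The first is "Ankle–brachial index (ABI) <0.9 or triglycerides ≥150 mg/dL and high-density lipoprotein cholesterol <40 mg/dL in men and <50 mg/dL in women". The second is a blood stasis score of at least 9 out of 32. Group I meets both and Group II meets the first only. The controls are defined by "Group III (normal): Does not meet either criterion from the aforementioned criteria". Nothing in these rules refers to current treatment.

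Section 2.4.2 names one treatment as a reason for exclusion: "Individuals currently on oriental medicine for the treatment of blood stasis". It also leaves room for discretion: "Individuals presenting with any other condition that could influence the assessment of this study, based on the investigator's discretion".

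Section 2.6 states that "the treatment to improve circulatory disturbance is not restricted during the study", and that "prescription medication other than Korean medicine should be recorded". The concomitant drug assessment is among the visit 1 procedures.

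Section 2.10 compares Groups I and II with Group III at visit 1 and describes Group III as being without circulatory disturbances. Analysis of covariance is to be used where needed; the examples given are sex, age, weight and height.

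**The concern.** The lipid part of criterion 1 reads the laboratory value as it stands on the day. Drug treatment can bring that value inside the cut-offs while the underlying disorder remains. The plan neither excludes nor restricts such treatment, and no stated grouping rule uses the drug record. Treated people can therefore be counted as normal.

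At stake is the main comparison. Section 2.7.1 puts forward resistin, serum amyloid P component, C-reactive protein and D-dimer as candidate diagnostic indicators. If some controls are treated members of the disturbed population, the contrast in these markers mixes disease status with treatment status. A useful marker could look weaker than it is. The blood stasis score and ABI are held within limits in Group III by the grouping rule itself, so the problem lies chiefly with the four markers.

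**Working it through.** **Step 1. Trace a person through Section 2.4.1.** Take someone with ABI of at least 0.9 who, untreated, would have both high triglycerides and low HDL cholesterol. Compare the assignment with and without drug control of the lipids.

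| Blood stasis score | Lipids untreated | Lipids drug-controlled |
|---|---|---|
| Below 9 | Criterion 1 only: Group II | Neither criterion: Group III |
| 9 or more | Both criteria: Group I | Criterion 2 only: no defined group |

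Two things follow. Group III can gain only would-be Group II members, because it also requires a score below 9. And since the two lipid components are joined by *and*, bringing either one inside its cut-off is enough to leave the lipid part of criterion 1.

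**Step 2. Look for a rule that prevents this.** The named treatment exclusion in Section 2.4.2 concerns oriental medicine only. The discretionary exclusion speaks of conditions, not of drugs, and is not fixed in advance. Section 2.6 records prescription drugs but gives them no role in grouping. Section 2.10 could adjust for them but does not name them. None of these changes who is labelled normal.

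**Step 3. How large could the effect be?** There is no figure in the plan to reproduce. Section 2.9 gives a target of 100 and says that no effect-size calculation was made; it gives no group split and no dropout rate. Everything below is assumed and only illustrates the mechanism.

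Notation, in SD units with SD held at 1:
- δ1 and δ2: true marker shifts of Groups I and II from untreated normal people.
- f: share of Group III who are treated would-be Group II members.
- r: share of the Group II shift that they keep under treatment.

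The mean of Group III then moves by f·r·δ2, so:
- II versus III: δ2(1 − f·r)
- I versus III: δ1 − f·r·δ2
- I and II pooled (equal sizes) versus III: (δ1 + δ2)/2 × [1 − 2·f·r·δ2/(δ1 + δ2)]

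Power by the normal approximation, two-sided 5%: Φ(Δ/√(1/n1 + 1/n2) − 1.96), where Δ is the observed difference.

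II versus III, 33 per group, r = 1:

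| f | Δ if δ2 = 0.7 | Power | Δ if δ2 = 0.5 | Power |
|---|---|---|---|---|
| 0 | 0.70 | 0.812 | 0.50 | 0.528 |
| 10% | 0.63 | 0.725 | 0.45 | 0.447 |
| 20% | 0.56 | 0.624 | 0.40 | 0.369 |
| 30% | 0.49 | 0.512 | 0.35 | 0.295 |

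Other values of r, with f = 20% and δ2 = 0.7:
- r = 0.5: Δ = 0.7 × (1 − 0.10) = 0.63, power 0.725.
- r = −0.5 (treatment takes the marker past the untreated normal level): Δ = 0.7 × (1 + 0.10) = 0.77, power 0.879. The contrast widens.

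Pooled, 67 versus 33, average shift 0.7, r = 1, f = 30% (power 0.908 at f = 0):
- δ2 = δ1: factor 1 − 0.30 = 0.70, Δ = 0.49, power 0.635.
- δ2 = δ1/2: factor 1 − 0.3 × 2 × 0.5/1.5 = 0.80, Δ = 0.56, power 0.750.
- δ2 = 0 (marker follows blood stasis only): factor 1, no dilution.

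These figures also ignore drug use within Groups I and II, which could shift the contrast either way.

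**The case against.** The other side has real points.

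- Unrestricted treatment belongs to an observational study, and the sentence in Section 2.6 concerns the study period, while the comparison is made at visit 1, within 7 days of registration. This stands: the sentence is not itself an error. The weight rests on the Group III definition and on the single named treatment exclusion.
- The covariate examples in Section 2.10 form an open list, and a full covariate list may be in an analysis plan that is not shown. This also stands. A reader might infer that drug use will go unadjusted; the document does not say so. But adjustment leaves the grouping rule as it is, and that rule is stated in full.
- The investigator may exclude people whose condition could influence the assessment. That may catch some of them, but not by a fixed rule.
- The protocol may define disturbance by current measured values, so that a person with controlled lipids is simply not disturbed. That is a coherent definition. It sits less well with a control label of normal and with evaluating diagnostic markers against it. The protocol also already removes people taking one kind of treatment.

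Three stronger readings are tempting. First, a reader might count people with hypertension or diabetes in Group III as misclassified, since the Introduction lists "hypertension, cardiovascular diseases, diabetes, hyperlipidemia, and arteriosclerosis" as probable causes of circulatory disturbance. Section 2.4.1, however, defines cases by ABI or lipids; a person with hypertension who meets neither is not a case under the protocol's own definition. Second, a reader might suppose particular drug effects on particular markers; the document says nothing about this. Third, a reader might take the controls to be contaminated as a matter of fact. No passage shows that any treated person will be in Group III, or how many.

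**Conclusion.** The point holds in a limited form. The stated grouping rule can place treated would-be Group II members among the controls, and nothing stated in the protocol article prevents it. The expected result is a marker contrast biased, usually, toward no difference.

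The size is unknown. It depends on the share of treated people in Group III, on how much of the marker shift they keep, and on how far each marker differs in Group II at all. If a marker tracks blood stasis alone, there is no dilution; if treatment moves a marker beyond the untreated normal level, the contrast grows. A reader might take the power figures as the loss this study will suffer. They are not: effect size, group split and treated share are all assumed, and this exploratory study makes no power claim. The correction is worth making because it is cheap and concerns the reference group for the main comparison.

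**What to change.** Either of two changes would do.

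1. **Section 2.4.1, grouping.** State that recorded current drug treatment for raised triglycerides counts as meeting the triglyceride component, and that for low HDL cholesterol counts as meeting the HDL component. Keep the *and*: the lipid part of criterion 1 is met only when both components are met, each by measurement or by treatment. Letting treatment for one component satisfy the whole lipid part would be a looser rule for treated than for untreated people. This option also gives a group to treated people with a score of 9 or more who would then meet criterion 1.
2. **Section 2.10, analysis.** Keep the grouping and pre-specify a sensitivity analysis of the four markers that excludes from Group III anyone on recorded lipid-modifying drugs and includes such use (yes/no, all groups) as a covariate in the analysis of covariance. After the exclusion, Group III has no users and the drug coefficient comes from Groups I and II alone, so it is sensible to report the adjusted model without the exclusion as well.

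Do not go further and drop people with other diagnoses from Group III only. That would make the controls unusually healthy and could exaggerate marker separation, and Section 2.6 does not list a diagnosis history among the data collected.

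Cost: both options use the concomitant drug record already taken at visit 1. The first also needs to know which lipid component a drug was given for, which the article does not say is recorded. Group III becomes slightly smaller, and the second option adds one analysis.
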